**Fig. 4 Fig4:**
[figure not shown]
Schedule of enrolment, interventions, and assessments. SPIRIT recommendation. Legend: t-1, before allocation; t0, allocated; t1, baseline; t2, post-intervention; t3, post-follow-up; CPh, conventional physical therapy; TUG, Timed Up and Go; DGI, Dynamic Gait Index; FSS, Fatigue Severity Scale; 6MWT, 6-min walk test

##### Secondary outcomes

The qualitative assessment about motivation, health empowerment, and the dependency of professional supervision at post follow-up period will be done by two researchers during an in-person interview, in a private room, and recorded for further transcription line-by-line and analysis. The questions will follow investigating the motivation in different steps of the study and are described in Table 3:

**Table 3 Tab3:** Distribution of questions in the study steps

Steps	Week	Question
Baseline	0	1. What made you seek physical therapy? 2. What does Parkinson’s disease mean in your life? 3. What are your expectations with physiotherapy?
Post-intervention	8	4. What this physiotherapy program meant in your life? 5. What did you think about the physiotherapy program that you participated? 6. After physical therapy, do you think you will be able to perform the exercises at home after discharge? What made you feel more or less capable? 7. Now at the end of the supervised treatment, what is your opinion of the expectations that you had at the outset?
Post follow-up	12	8. Were you able to do this exercise without supervision in your daily life? a) How was your experience? b) If you cannot do, what were the reasons? 9. After this period without supervision, what has this physiotherapy program meant in the last months of your life? 10. After your participation in this study, the reasons that make you seek physiotherapy are the same?

Note: Script assembled after pretest and familiarization with three individuals with PD.

The quantitative outcomes will investigate the preliminary effectiveness of the EMPOWER-PD on mobility, gait, fatigue, and aerobic function/endurance. Mobility will be assessed by the Timed up and Go test (TUG) which consists in walk a distance of 3 m, go beyond the horizontal mark located on the floor, turn on its axis, and return to sit again on the same chair. The time of all tasks will be timed and classified according to falls risk for PD individuals (< 11 s) [40, 41].

Gait will be evaluated by the Dynamic Gait Index (DGI) that assesses the gait in different sensorial contexts for eight tasks, which will be classified in a score of 0 to 3. The maximum score is the 24 points indicating a gait performance capable of adapting the different demands proposed by the test [42].

To assess the fatigue, we will use the Fatigue Severity Scale (FSS). The scale evaluates the impact of fatigue on motivation, exercise, physical functioning, accomplishing tasks and responsibilities, and interfering with work, family, or social life. Contains 9 items, in which the rating scores range from 1 to 7 for each statement. The highest scores (maximum 63 points) indicate more severe fatigue [43].

The 6-min-walk test (6MWT) will quantify the aerobic function/endurance. The participants will walk 30 m for 6 min, spinning the cones positioned in the final 50 cm after the starting and finishing point of the track. The total number of laps is multiplied by 60 (30 m + 30 m) and added to the distance in meters from the last lap resulting in the total distance covered in the test [44, 45].

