Based on all information above, this study presents the EMPOWER-PD protocol, a physical therapy approach based on the individual preferences. As a new intervention protocol, it is necessary to verify it feasibility when applied to the target population. This study presents the design of the feasibility randomized controlled trial that aims to(i)Investigate the feasibility of the EMPOWER-PD protocol through adherence rate, recruitment rate, and safety.(ii)Compare the preliminary effectiveness of the EMPOWER-PD with the conventional physical therapy through qualitative analysis of motivation, empowerment of health, followed by the analysis of the dependency of professional supervision by individuals to remain active in the post follow-up period.(iii)Compare the preliminary effectiveness of the EMPOWER-PD in motor and non-motor symptoms (functional mobility, gait, fatigue, aerobic capacity/endurance) with the conventional physical therapy through quantitative analysis of estimates of 95% confident interval.

We hypothesize that the EMPOWER-PD will lead to higher adherence and safety when compared with conventional physical therapy. Concerning motivation, health empowerment and dependency of professional supervision by individuals to remain active in the post follow-up period, we hypothesize that the EMPOWER-PD will be associated with better outcomes in preliminary effectiveness than the conventional physical therapy. For the motor and non-motor symptoms, we hypothesize that the EMPOWER-PD will be associated with similar preliminary effectiveness to the conventional physical therapy.

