Specifically, in the last 2 weeks of the protocol (seventh and eighth weeks), the fourth pillar of EMPOWER-PD (winning autonomy and power for an active life), will be composed by a booklet (Additional file 3) with circuit images and suggestions of dynamics and progressions (already done in weeks 1 to 6 of the protocol) that will be chosen by the participant based on their preferences. The booklet will be formulated by the therapist according to the information from the group collected by contact with them in all sessions, being adapted for each population that receive the EMPOWER-PD. It will be composed of multiple choice options of stretching, main part, progression, preferences, and cooling; all chosen according to the group previously at the beginning of the activity. Throughout the sessions of the last 2 weeks, the therapist will become less active in the stages of construction of the exercises, duration, and frequency of the exercise, passing such responsibility to the individuals themselves. The intervention will continue to be supervised, but the therapist will be present as a source of guidance stimuli for the group, how initially controlling the time of each part, suggesting the time to progress and others according to the necessity of the group.

The warm-ups will always count on varied exercises that stimulate the activation of the body’s own perception and the relationship between the groups. The exercises will use music, interaction with their own body and their colleagues, and their suggestions of warm-up exercises based on their own knowledge about physical activity previously practiced. A “back to calm” stage will feature breathing and meditative exercises with the goal of to perceive sensations in their body after the exercise. In addition to the feedback provided after each task, at the end of each session, a talk wheel is held about their perceptions of the session and the repercussion under their daily routine.

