### Procedures

The baseline assessment will be conducted once participants have given informed consent. All interviews/scales will be applied individually in a private setting by a blinded researcher, and all participants will receive an identification number. All evaluation will be performed in the afternoon, with individuals on the “on” phase of the medication. Demographics and eligibility criteria information will be collected at the baseline step. From there, the volunteers eligible in the inclusion criteria will be randomized into one of the two groups (EMPOWER-PD group and conventional physical therapy group) by a second researcher not involved in other steps.

Participants allocated to both groups will receive 8 weeks of intervention that will occur at the same time in different places to minimize individuals’ awareness of the differences between interventions. Then, the participants will be assessed at post-intervention, always by the same physiotherapist research, followed by a follow-up period of 4 weeks. The main objective of this stage of the study is to verify if the intervention would be a source of motivation/empowerment of health for a more proactive life, and in this way, decrease the dependency of professional supervision to remain active. For this, the participant will remain 4 weeks without any guidance from the therapist. After this, they will be contacted by phone to schedule the final evaluation, which will be performed on all outcome variables of the others stages of the study. Participants who drop out of the study will also be contacted by phone for the final evaluation.

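### The unsupervised follow-up stage is about remaining active, but the only question on actual behaviour concerns the trained exercise and has no baseline counterpart

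*Protocol article*

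**What the plan says.** The Procedures section says the unsupervised stage should show whether the intervention is a source of motivation and empowerment and would in this way "decrease the dependency of professional supervision to remain active". Objective (ii), at the end of the Background, is a comparison of arms: "Compare the preliminary effectiveness of the EMPOWER-PD with the conventional physical therapy through qualitative analysis of motivation, empowerment of health", followed by "analysis of the dependency of professional supervision by individuals to remain active in the post follow-up period".

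Table 3 (Secondary outcomes) sets out the interview questions by study step, and its note says the script was assembled after a pretest:

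- **Week 0:** three questions, on why the person sought physiotherapy, what the disease means to them, and "What are your expectations with physiotherapy".
- **Week 8:** four questions. The relevant one is about anticipation: "do you think you will be able to perform the exercises at home after discharge".
- **Week 12:** three questions. Question 8 is "Were you able to do this exercise without supervision in your daily life", with probes on the experience and, for those who could not, "If you cannot do, what were the reasons". Question 9 asks what the programme has meant after the period without supervision. Question 10 asks whether the reasons for seeking physiotherapy are unchanged.

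Under Data management and analysis, the transcripts go to thematic content analysis. No score or coding rule for dependency is given.

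**The concern.** Two features of the script fall short of the aim.

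**Scope.** The aim concerns staying active in general. Question 8 concerns the trained exercise, which in both arms is a group circuit with an 8-m track, chairs of graded height and obstacles (Tables 1 and 2). EMPOWER-PD steers participants towards pleasurable activities of their own choosing. Someone who followed that lead and took up walking or dancing alone could truthfully answer no.

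**Timing.** Speaking of a decrease implies a starting point. Nothing in the week-0 script records whether a participant was already active without a professional, so a person whose habits changed cannot be told from one whose habits did not.

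At stake is the interpretation of one secondary, qualitative outcome. It is, however, the outcome for which the four unsupervised weeks were designed. Thematic analysis can only work on what participants were asked or happened to volunteer.

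**Working it through.** The protocol states no figure on this point, so the check is mainly a reading of the script against the aim. A short calculation then shows why starting status matters at this sample size.

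**1. Construct against item.** Objective (ii) and Procedures: dependence on supervision to remain active. Table 3, question 8: ability to do the trained exercise unsupervised. The second is a subset of the first. None of the other nine questions asks about other physical activity.

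**2. Timing.** Week 0: no item on unsupervised activity. Week 8: expected ability to do the exercises at home, not behaviour. Week 12: actual behaviour, once. Within-person change needs the same item at two times, and there is one.

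**3. Could another source fill the gap?**
- The Timed Up and Go, Dynamic Gait Index, Fatigue Severity Scale and 6-min walk test measure performance or fatigue, not habitual activity.
- The Empower-PD section describes a pre-treatment anamnesis on routine and free time. It is taken by the treating physiotherapist to plan sessions and is described for that arm only, so it gives no comparable baseline.
- Procedures mentions demographics at baseline without listing them. I assume they do not include unsupervised exercise; if they do, part of the gap closes.

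**4. Chance imbalance in starting status (illustration).** Inputs: n = 12 per arm (Sample size section); p = share already active unsupervised at week 0, not given, so taken as 0.2 to 0.7. Randomisation is stratified by sex and Hoehn and Yahr stage only; the calculation ignores this.

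With X and Y independent Binomial(12, p), one per arm:

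P(|X − Y| ≥ 3) = sum of P(X = i)·P(Y = j) over all i, j with |i − j| ≥ 3.

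| p | P(imbalance of 3 or more people) |
|---|---|
| 0.2 | 0.197 |
| 0.3 | 0.263 |
| 0.5 | 0.307 |
| 0.7 | 0.263 |

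Three people are 3/12 = 25 percentage points of an arm.

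**5. Strength of a week-12 contrast (illustration).** If the week-12 answers were tabulated as proportions, which the protocol does not plan, the standard error of the difference with a common share p would be √(2p(1 − p)/12).
- p = 0.2: √(0.32/12) = 0.163; 95% half-width 1.96 × 0.163 = 0.32.
- p = 0.5: √(0.50/12) = 0.204; 95% half-width 1.96 × 0.204 = 0.40.

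A contrast at week 12 is therefore available but imprecise, and without a baseline item nobody can see whether the arms started alike.

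**The case against.** **The objective does not need a change score.** Objective (ii) compares randomised arms in the post follow-up period, and the hypothesis is of better outcomes than under conventional therapy. A reader might infer that without a baseline item no reduction in dependency can be shown at all. The documents do not support that: a randomised contrast at week 12 can indicate lower dependency relative to control. This objection stands. What is lost is individual change and any check on starting status.

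**The interview is open.** A reader might infer that people active in other ways will be classed as dependent. No rule codes a no to question 8 that way. The probes ask about experience and reasons, and questions 9 and 10 are broad, so other activity may surface. This also stands, and the fault is a risk of missing information rather than a fixed misclassification. But whether a participant mentions other activity is left to chance.

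**The question does not plainly favour EMPOWER-PD.** That arm has a "booklet (Additional file 3) with circuit images and suggestions of dynamics and progressions" and rehearses choosing exercises in weeks 7 and 8. A reader might infer that its exercise was handed over in portable form. The text describes the booklet's use in supervised sessions and does not say it goes home. Practising self-direction is also part of the intervention under study, so a benefit from it is an effect, not a bias.

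**Prior habits do not simply inflate question 8.** If the item means the trained circuit, someone who already walked alone does not become a yes. One cannot argue both that earlier walkers count as successes and that walkers answer no.

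**Larger imbalance figures mislead.** If 4 or 8 of the 24 were already active, the chance that the arms differ by at least 2 is 1 − 66²/10,626 = 0.59 or 1 − 495²/735,471 = 0.67. With an even total split between two arms the difference is always even, so this means only that the arms are not exactly equal. It does not establish a 17-point (2/12) bias in an outcome never planned as a proportion.

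**Conclusion.** The point holds in limited form. The only question on actual unsupervised behaviour is narrower than the stated construct, and it has no week-0 counterpart. Other forms of activity may be missed, and individual change from baseline cannot be documented. The between-arm comparison at week 12 survives, but with 12 per arm it is weak and cannot be checked against where participants started.

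The size cannot be taken from the protocol. The imbalance probabilities of about 0.20 to 0.31 rest on an assumed 20% to 70% already active alone, on independent binomial counts, and on ignoring the stratification. They show why starting status is worth recording and do not estimate a bias. The primary feasibility outcomes are unaffected. The change is worth making because it is cheap and concerns the question the follow-up stage exists to answer.

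**What to change.** 1. **Week 0:** add one open question on what physical activity or exercise the person did without a professional in the last 4 weeks, and how often.
2. **Week 12:** ask the same question before question 8. Its 4-week window matches the unsupervised period.
3. **Keep question 8** as the item on the trained exercise.
4. **Report two results separately:** whether the person remained active, and whether they did the trained exercise. Use the week-0 answers to interpret the comparison of arms within the planned thematic analysis; no score is needed.

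If the baseline question cannot be added, broaden the week-12 wording to any physical activity and state the aim only as a comparison between arms at week 12.

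The cost is a few extra minutes in two interviews already scheduled, and some additional transcription and coding.

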### Procedures

The baseline assessment will be conducted once participants have given informed consent. All interviews/scales will be applied individually in a private setting by a blinded researcher, and all participants will receive an identification number. All evaluation will be performed in the afternoon, with individuals on the “on” phase of the medication. Demographics and eligibility criteria information will be collected at the baseline step. From there, the volunteers eligible in the inclusion criteria will be randomized into one of the two groups (EMPOWER-PD group and conventional physical therapy group) by a second researcher not involved in other steps.

Participants allocated to both groups will receive 8 weeks of intervention that will occur at the same time in different places to minimize individuals’ awareness of the differences between interventions. Then, the participants will be assessed at post-intervention, always by the same physiotherapist research, followed by a follow-up period of 4 weeks. The main objective of this stage of the study is to verify if the intervention would be a source of motivation/empowerment of health for a more proactive life, and in this way, decrease the dependency of professional supervision to remain active. For this, the participant will remain 4 weeks without any guidance from the therapist. After this, they will be contacted by phone to schedule the final evaluation, which will be performed on all outcome variables of the others stages of the study. Participants who drop out of the study will also be contacted by phone for the final evaluation.

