**Method:**

A 12-week pilot for a randomized clinical trial will assess the feasibility and preliminary effectiveness of the EMPOWER-PD and make comparisons with conventional physical therapy (CPh). Both protocols consist of mobility and locomotion training, and aim at improving motor and non-motor symptoms through different approaches. The EMPOWER-PD aims to provide a source of motivation and empowerment of health through the self-knowledge of the individual’s abilities and limitations, in a protocol that addresses individual preferences. The CPh is based only on physiotherapist decisions, not addressing the individual’s preferences or motivation/empowerment. The target recruitment will be 24 PD individuals, between stages I and III of Hoehn and Yahr (HY), who will be recruited from Brazilian Parkinson’s disease Rehabilitation Initiative (BPaRkI) with allocation ratio 1:1. A computerized block randomization procedure will be implemented by a blinded researcher with the participants blinded to group assignment. The sessions will be conducted in a group setting, twice a week, during 60 min for 8 weeks, followed by 4 weeks of follow-up. The primary outcomes will be the feasibility data (adherence, recruitment rate, and safety). The secondary outcomes will assess the preliminary efficacy on qualitative assessment about individual’s motivation/empowerment and quantitative motor outcomes (Timed Up and Go and Dynamic Gait Index) and non-motor symptoms (6-min walk test and Fatigue Severity Scale). The recommendation to have 6–12 participants per group will be adopted based on the qualitative analysis to the sample size.

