#### Sample size

The primary outcome of this pilot for a randomized clinical trial will be the feasibility (adherence, recruitment rates and safety). As in feasibility studies a formal sample size calculation is not required [30], we estimated the number of participants based on qualitative analysis. We will adopt the recruitment of 6–12 participants per group as a recommended for qualitative studies, being adopted the major value (*n* = 12 per group) [31]. Accordingly, we will use the criteria of sampling saturation that means “collecting data until no new information is obtained” [32].

In relation to the quantitative variables, the present study is not intended to be fully powered for detection of statistically significant effects, but it will enable a sample size calculation related to the quantitative variables for a future randomized trial [33]. For that, we plan to select the sample size based on reasonable precision of estimates of standard deviation of quantitative measures which have shown sensitivity in this feasibility study.

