### Data management and analysis

For the feasibility analysis, the results will be expressed as percentage and numbers referring to adherence, recruitment rates, and safety, respectively. After qualitative data collection, two authors will perform the total transcription of the audios and notes line-by-line. Then, two authors will start the codification of the *corpus.* After transcription, the corpus will be codified in numbers and their respective groups (e.g., # ID1emp, # ID5cph) by a blinded third researcher, for the later analysis by a fourth researcher. Codes will then be consolidated into categories after an extensive exploration of the material and interpretation of the data obtained according to thematic analysis of the content. From this, entire research team will discuss to formulate inferences.

To verify the preliminary effectiveness regarding quantitative outcomes, the descriptive analysis will be performed with frequency, central tendency, and variability (mean and standard deviation or median and interquartile interval) in the statistical program SPSS 20.0 for Windows (IBM-USA). All results of the preliminary efficacy of the feasibility trial will be described as estimates of 95% confidence interval. An intention-to-treat analysis will be done with participants including who eventually will be missed in any part of the study.

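### The only stated call-back for participants who drop out is for the week-12 evaluation, so week-8 outcomes and interview answers for those who stop during treatment are not secured

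*Protocol article*

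**What the plan says.** Procedures sets out the order of events: 8 weeks of intervention, an assessment, 4 weeks without guidance, and a final evaluation. On the first assessment it says: "Then, the participants will be assessed at post-intervention, always by the same physiotherapist research, followed by a follow-up period of 4 weeks". On the last it says that after the unsupervised weeks "they will be contacted by phone to schedule the final evaluation, which will be performed on all outcome variables of the others stages of the" [trial]. The rule for those who leave follows: "Participants who drop out of the study will also be contacted by phone for the final evaluation". No other contact with them is described.

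Data management and analysis promises: "An intention-to-treat analysis will be done with participants including who eventually will be missed in any part of the study". It also says: "All results of the preliminary efficacy of the feasibility trial will be described as estimates of 95% confidence interval".

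Table 3, under Secondary outcomes, assigns each interview question to a step. Questions 4 to 7 belong to week 8. They cover what the programme meant, the participant's opinion of it ("What did you think about the physiotherapy program that you participated"), whether the participant feels able to exercise at home, and how the initial expectations look in hindsight. Questions 8 to 10 belong to week 12. Primary outcomes leaves the acceptability of the protocol to the qualitative analysis.

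**The concern.** Week 8 is the only measurement taken directly at the end of the supervised programme. Week 12 comes after 4 weeks without guidance and answers a different question. If a participant who stops in, say, week 3 is next contacted for week 12, the week-8 tests are not done and the week-8 questions are not asked.

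Two things are at stake. The first is the between-arm comparison at week 8. The Background hypothesises higher adherence with EMPOWER-PD. If that is right, absence at week 8 will be more frequent in the conventional arm, and the comparison will be between groups selected to different degrees. The standard deviations that the pilot is meant to supply for a future trial would come from the same reduced set.

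The second is acceptability. People who leave early are among the most informative about whether the programme is acceptable and why people do not continue, which the Discussion names as a purpose of the interviews. An analysis plan can specify how to handle a missing walking distance. It cannot recover an interview that was not held.

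**Working it through.** **Step 1: what each text secures for someone who stops during weeks 1 to 8.**

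| Item | Scheduled | Secured by the stated call-back? |
|---|---|---|
| TUG, DGI, FSS, 6MWT at week 8 | Post-intervention | No call-back stated |
| Questions 4 to 7 | Week 8 only (Table 3) | No call-back stated |
| TUG, DGI, FSS, 6MWT at week 12 | Final evaluation | Yes, if the person accepts |
| Questions 8 to 10 | Week 12 (Table 3) | Yes, if the person accepts |

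The final evaluation is said to cover all outcome variables, but that wording does not clearly override Table 3's assignment of questions to weeks. Question 9 overlaps question 4. Nothing at week 12 takes the place of question 5 or question 6.

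**Step 2: the plan's own figure.** Abstract, Method: "The target recruitment will be 24 PD individuals". Sample size gives 12 per group, and 2 × 12 = 24, so the total reproduces. It rests on a recommendation for qualitative studies, so there is no power calculation to check.

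**Step 3: how many could be affected (illustration).** Primary outcomes treats retention above 80% as feasible. With 24 participants, 20/24 = 83.3% meets this and 19/24 = 79.2% does not. If all 4 losses came before week 8, up to 4 people would lack week-8 data. If all 4 were in one arm, that is 4/12 = 33% of the arm.

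**Step 4: effect on precision (illustration).** The 95% half-width for a difference in means, in SD units, is t(0.975; n1 + n2 − 2) × √(1/n1 + 1/n2).

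- 12 v 12: 0.847 SD
- 10 v 10: 0.940 SD, which is 11% wider
- 12 v 8: 0.959 SD, which is 13% wider

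**Step 5: possible shift in the week-8 difference (illustration).** If m of 12 in one arm are unobserved and differ from those observed by d SD, leaving them out shifts that arm's mean, and so the difference, by (m/12) × d. The documents give no value for d, so 0.5 to 1.0 SD is an assumption.

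- m = 2: 2/12 × 0.5 = 0.08 SD, to 2/12 × 1.0 = 0.17 SD
- m = 4: 4/12 × 0.5 = 0.17 SD, to 4/12 × 1.0 = 0.33 SD

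**The case against.** The strongest case on the other side is that the text never says those who leave are called back only at week 12. It says that the participants are assessed at post-intervention and excludes nobody. For completers too, a phone call is mentioned only before the final evaluation, because by then contact has lapsed. The rule may simply extend that call to those who left, without withdrawing their week-8 visit. The document is also an article, and detail on retrieval may sit in a full protocol that is not shown. This stands in part: exclusion at week 8 is not established. But the authors did write a rule for people who drop out, and it names one visit. Staff following it as written would have no instruction to invite them at week 8.

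A reader might infer that the promised intention-to-treat result becomes a completers-only result, or that the week-8 comparison is biased by design. The documents support neither. The analysis section includes participants missed in any part of the study, no completers-only analysis is stated, and the handling of absent values may be left to an analysis plan. Bias would also require that those who leave are in fact untested, that they differ from the rest, and that the loss is uneven between arms. None of this is quantified.

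A reader might also take the 80% figure as a limit on losses. It is a criterion for going on to a larger trial, and it neither caps nor predicts dropout. Retention is defined in two ways: completion of all 16 sessions, and presence at each step. A person who misses one session fails the first definition yet may attend week 8. A person lost after week 8 already has week-8 data. So it is not true that every lost participant would lack week-8 data.

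Finally, those who return at week 12 provide all the outcome measures and are asked why they could not exercise unsupervised. Their absence at week 8 would itself show in the retention figures. These points limit the consequence but do not fill the week-8 gap.

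**Conclusion.** The point holds in a limited form. As written, the procedures do not secure week-8 tests or answers to questions 4 to 7 for anyone who stops during weeks 1 to 8. The week-8 between-arm estimates and the acceptability interviews are therefore at risk of resting on those still attending, and the missingness may differ by arm if the adherence hypothesis is right.

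The size is modest. The gap concerns one time point. The outcomes affected are secondary, reported descriptively with confidence intervals, and not meant to be fully powered. The figures of 4 of 24, an interval 11 to 13% wider and a shift of 0.08 to 0.33 SD are illustrations. They assume that 2 to 4 people stop before week 8 and are not tested then; the shift also assumes that they are in one arm and differ from the others by 0.5 to 1.0 SD. The qualitative loss matters more than the quantitative one, because no analysis can repair it and the sample size itself was set on qualitative grounds.

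**What to change.** Change the rule in Procedures so that participants who stop attending sessions, unless they withdraw consent, are invited to both the week-8 and the week-12 evaluations on the original calendar. Questions 4 to 7 are asked in person at week 8 or, if that visit is missed, at the next evaluation. Secondary outcomes specifies an in-person, recorded interview in a private room, so any interview held by phone should be recorded as a change of mode.

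The cost is one or two sentences and a few extra invitations to visits already scheduled. Some who stop will decline, so the change reduces the gap without closing it. Answers to questions 4 to 7 given at week 12 would also be more retrospective than those given at week 8. If the investigators already intend to see everyone at week 8, the sentence only removes the ambiguity.
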